### Measures

#### Primary Outcome

Our primary outcome is adherence to all 3 of the 24-hour Movement Guidelines. Preschoolers’ PA and sleep were assessed in 15-second epochs using the Actigraph GT3X+ accelerometer. Preschoolers wear this device on their wrist using a Velcro band, only removing it for water-based activities (eg, bath). Accelerometer data will be evaluated using the Sadeh algorithm to detect sleep periods and compared with the parent-report of sleep [33]. Periods of ≥20 minutes of continuous zeroes during the day will be removed as nonwear time [34,35]. Validated cut points for wrist measurement in this age range will be used for sedentary behavior (0-328 counts per 5 seconds), light PA (329-1392 counts per 5 seconds), and MVPA (≥1393 counts per 5 seconds) [36]. Total PA is the sum of light PA and MVPA. Preschoolers with ≥3 days (at least 1 weekday and 1 weekend day) of ≥10 hours of wear, and 3 days of sleep, will be included for analysis, similar to another wrist-worn protocol [37], and is the estimated minimum for accelerometer wear in this age range [38,39]. To capture adherence to the sedentary screen time guideline, parents are asked, “On an average 24-hour period, how much time does your child spend using electronic screen devices (such as a smartphone, tablet, video game, or watch television or movies, videos on the internet) while they are sitting or lying down?” with a free response option. This question is conducted at screening and subsequent visits and was chosen to align with surveillance efforts of movement behaviors [40]. This questionnaire reflects the previous week before accelerometer wear. The sum of guidelines obtained based on these measures, and if the participant meets all 3 guidelines, will be used for analysis.

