#### Exploratory Outcomes

##### Parent Report of 24-Hour Guideline Adherence

Parents will report how many days per week (range: 0-7) their child obtains at least 180 min/d of total PA and at least 60 min/d of MVPA. Staff members describe total PA as including any activity, such as slow or easy movement, based on direct report observations of preschooler’s movement [42]. These may include walking, light dancing, playing catch, and easy bike riding. MVPA includes any “huff and puff” activity that increases their heart rate, such as playing a sport, more intense dancing, and running. If parents have trouble discerning days, the staff will ask them about the past week. Furthermore, parents will be asked on average how much overnight sleep and time their child spends napping, in separate questions with free response options, which are summed for a total amount of sleep during the day. The sleep questions have demonstrated moderate correlations with accelerometry measures [43]. Parents are also asked about screen time (refer to “Primary Outcomes” section). We chose these questions based on national surveys of child PA [44] and surveillance efforts of child movement behaviors [40,45]. This information is gathered during the phone screening process, where trained staff members ensure parents consider both weekdays and weekends, and any changes due to nontypical weeks, to obtain accurate habitual behavior amounts. Screening questions related to total PA, MVPA, and sleep are repeated at week 6 and week 12.

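### Physical activity is recorded in 15-second epochs but scored with cut points in counts per 5 seconds, and no conversion is stated for this component of the primary outcome

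*Protocol article*

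**What the plan says.** Under Measures, Primary Outcome, the protocol article says that preschoolers' PA and "sleep were assessed in 15-second epochs using the Actigraph GT3X+ accelerometer". The same paragraph then gives intensity limits that it describes as validated for wrist wear in this age range: "sedentary behavior (0-328 counts per 5 seconds), light PA (329-1392 counts per 5 seconds") and "MVPA (≥1393 counts per 5 seconds"). It adds that "Total PA is the sum of light PA and MVPA". The unit is 5 seconds for every limit, and no section links it to the 15-second epoch.

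Participants, Eligibility, and Recruitment defines the PA guideline as at least 180 min/d of total PA, of which at least 60 min/d is MVPA. The primary outcome is meeting all three guidelines, and Aim 1 compares that proportion between arms at 12 weeks.

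On daytime sleep, the Primary Outcome section names the Sadeh algorithm for detecting sleep periods. It then says that daytime spells of 20 or more "minutes of continuous zeroes during the day will be removed as nonwear time". Naps are mentioned only in the exploratory parent-report measure, where overnight and nap times are asked separately, "which are summed for a total amount of sleep during the day".

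**The concern.** A cut point belongs to the epoch in which it was derived. The article states an epoch and a set of limits that do not match, and leaves out the step that would reconcile them. This goes beyond condensing, because both values are printed and they cannot both be used as they stand.

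PA is one of three conditions that a child must meet to count as a success. If the epoch choice moves minutes across the 60-minute or 180-minute line, it changes who is adherent on PA and so who can be adherent on all three. If the choice stays open until outcome data are in hand, the primary endpoint also carries an avoidable analytic option.

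**Working it through.** **Inputs.** From Primary Outcome: epoch 15 s; light PA starts at 329 counts per 5 s; MVPA starts at 1393 counts per 5 s; total PA = light PA + MVPA. From Participants, Eligibility, and Recruitment: at least 180 min/d total PA including at least 60 min/d MVPA. Assumption: a 15-second count is the sum of three consecutive 5-second counts. The plan states no figure for the conversion, so there is none to reproduce.

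**Step 1. Ratio of the units.** 15 s / 5 s = 3.

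**Step 2. Limits used unscaled on 15-second counts.** As a rate per 5 s, the effective limits are:
- light PA: 329 / 3 = 109.7, about 110, inside the plan's own sedentary band (0-328);
- MVPA: 1393 / 3 = 464.3, about 464, inside the plan's own light-PA band (329-1392).

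The direction is certain. If any 5-second count in a window reaches a limit, the 15-second sum reaches it too, and the whole 15 seconds is credited. Unscaled scoring can therefore never give fewer minutes of total PA or MVPA than 5-second scoring.

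**Step 3. Limits multiplied by 3.** 329 × 3 = 987 and 1393 × 3 = 4179 counts per 15 s. This restores the average rate but classifies three 5-second periods as one.

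**Step 4. Small patterns.** These are constructed from the stated limits to show direction. They are not estimates of what children do.

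| Three 5-s counts | Sum | Scored at 5 s | 15 s, unscaled | 15 s, limits × 3 |
|---|---|---|---|---|
| 110, 110, 110 | 330 | 15 s sedentary | 15 s light | 15 s sedentary |
| 465, 465, 465 | 1395 | 15 s light | 15 s MVPA | 15 s light |
| 1393, 0, 0 | 1393 | 5 s MVPA, 10 s sedentary | 15 s MVPA | 15 s light |
| 329, 329, 328 | 986 | 10 s light, 5 s sedentary | 15 s light | 15 s sedentary |

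Row 3 under × 3 turns 5 s of total PA into 15 s and loses the MVPA. Row 4 under × 3 turns 10 s of total PA into none. Scaling is therefore not equivalent to 5-second scoring, and its net effect depends on how activity alternates with rest within 15 seconds. The documents give nothing from which to estimate that, so no number of minutes is offered here.

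**Step 5. Link to the endpoint.** Both guideline lines (180 and 60 min/d) are read from these classified minutes. A child near either line can change PA status, and hence all-3 status, with the choice of scoring alone.

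**The case against.** The best defence is that the unit is printed beside every limit, so a competent analyst would not apply 5-second limits to 15-second sums. The limits could be read as rates and scaled, or the files could be re-integrated to 5 seconds. Scoring is also the same in both arms, and an article condenses a fuller protocol.

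Much of this stands. The gap is an unfixed step, and nothing shows that the unscaled error will be made. Common scoring means that the mismatch does not by itself favour an arm. But the defence names two different repairs, the text chooses neither, and they need not give the same PA minutes. Condensing does not account for two stated values that do not match.

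A reader might infer several stronger things that the documents do not support:
- *That PA cannot be scored at all.* It can, once the epoch and limits are matched.
- *That nearly every child would pass the PA guideline.* This assumes both unscaled use and a distribution of counts that the documents do not give.
- *That the nonwear rule deletes naps and so costs power.* Sadeh detection is named before the zero-count rule, no order that removes naps first is fixed, and an activity or sleep log is collected with each wear period (Baseline Visit; Follow-up Visits). Only unbroken runs of zeroes would be at risk. No figure says how many children depend on naps to reach 10 hours, so a power loss cannot be derived.

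**Conclusion.** The point holds for the epoch mismatch. The stated 15-second epoch and the stated per-5-second cut points do not fit together, and they determine one of the three components of the primary outcome. Only the factor of 3 and what follows from it are firm: effective limits of about 110 and 464 counts per 5 s if unscaled, with PA and MVPA minutes that can only rise; 987 and 4179 per 15 s if scaled, which is a different rule from the validated one and can shift total PA in either direction. The size of the effect in minutes, in children reclassified or in power cannot be stated from the document. The conclusion rests on counts being additive across epochs and on no conversion being described elsewhere in the article.

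The nap question is a secondary clarification. The article does not say in which order sleep detection and nonwear removal are run, or whether device-detected naps count toward 10-13 h/d. That is open, but it is not an error.

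**What to change.** In Primary Outcome, state one epoch for PA with matching cut points, and do so before analysis:
1. Preferred: re-integrate the stored device files to 5-second epochs for PA and apply 329 and 1393 unscaled. This assumes that raw files, or files at 5 seconds or finer, are kept; the article does not say so.
2. If only 15-second data exist, replace the limits with cut points validated at 15 seconds and cite them. Do not simply multiply the present limits by 3.

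Apply the same processing to baseline, week 6 and week 12 in both arms.

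As a clarification, add a sentence saying that daytime sleep is identified with the Sadeh algorithm and the log before the 20-minute zero-count rule is applied, and whether device-detected naps count toward the 10-13 h/d guideline.

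The cost is reprocessing files already collected and a short text change. No new data collection or visits are needed. There is time: recruitment is expected to run to December 2026, and 28 families had completed the final visit by October 2025.

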### Participants, Eligibility, and Recruitment

To be included, parents must report that their preschooler meets zero or 1 guideline for PA, sleep, and screen time as defined by the World Health Organization at the screening call [1]. Zero or 1 guideline was chosen as existing prospective studies demonstrate meeting 1 or zero guidelines is associated with lower motor skills and cognitive development compared with meeting all 3 guidelines [5,24]. Based on work conducted before the COVID-19 pandemic, we anticipated 15%-20% of preschoolers would qualify [5], with similar proportions found in a preschooler-focused systematic review [4]. Adherence to the 24-hour Movement Guidelines by parent report was chosen to reduce the burden, align with a survey study that informed analysis [25], and ensure the inclusion of the target population. The PA guideline is defined as ≥180 min/d of total PA, including ≥60 min/d of MVPA. The sleep guideline is defined as 10-13 h/d. The sedentary behavior guideline is defined ≤1 h/d of sedentary screen time.

Parents must also agree to use their mobile phone for the study duration (approximately 12 weeks), download the mobile app onto their phone, be fluent in English, and be willing to travel to the research site to complete study visits. Exclusion criteria are mobility limitations as reported by the parent, meeting 2 or 3 of the 24-hour movement guidelines, sibling or household member participating in the study, and parents reporting the preschooler will not wear a device on their wrist.

This study seeks 80 families, with 40 families per arm. Parents of preschoolers (aged 3-4 y) are recruited from a metropolitan area of a Midwest US state. We plan to recruit through the institution’s research-based list-serves (including local children’s hospitals), a local advertisement through social media, blogs, magazines, community-based efforts (eg, childcare centers and local events), and at local medical centers. Recruitment efforts include flyers and paid advertisements.

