#### Recruitment Plans

We will use various existing modalities of recruitment in the selected area to ensure the recruitment amount is achieved. As part of this 12-week study, participants are contacted every 2 weeks or up to 1 month to schedule visits and pick up accelerometers. All available data will be sought in the case of discontinuation after visit 1, with the priority of 24-hour movement behavior data (questionnaire and accelerometry), other questionnaires, then anthropometry, cognition and motor skill assessments.

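### The valid-wear rule, as written, discards week-12 outcomes that one failed guideline has already settled as not met

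*Protocol article*

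**What the plan says.** Under Primary Outcome the protocol states: "Our primary outcome is adherence to all 3 of the 24-hour Movement Guidelines". Activity and sleep come from the wrist accelerometer. The inclusion rule begins "Preschoolers with ≥3 days (at least 1 weekday and 1 weekend day" and continues "of ≥10 hours of wear, and 3 days of sleep, will be included for analysis". No exception is given.

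Screen time does not come from the device: "To capture adherence to the sedentary screen time guideline, parents are asked". On timing, "This questionnaire reflects the previous week before accelerometer wear". Under Participants, Eligibility, and Recruitment the cut-off is given: "The sedentary behavior guideline is defined ≤1 h/d of sedentary screen time". The section on follow-up visits has parents complete questionnaires at the week-12 visit, where the accelerometer is fitted for the two weeks that follow.

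The endpoint is then built from all of these: "The sum of guidelines obtained based on these measures, and if the participant meets all 3 guidelines, will be used for analysis". Aim 1 compares the all-three proportions at 12 weeks by chi-square and names no other analysis population. Exploratory Aims adds an intent-to-treat regression, and multiple imputation as a sensitivity analysis. Recruitment Plans says that all available data will be sought after discontinuation, "with the priority of 24-hour movement behavior data (questionnaire and accelerometry" coming first.

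**The concern.** Meeting all three guidelines is an and-type composite. It takes three observed successes to establish that it is met, but only one observed failure to establish that it is not. A requirement for valid activity and sleep data therefore suits a child who might have met all three. It is unnecessary for a child already known to have failed.

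Screen time is the component most likely to settle the matter. The sample-size section expects few children to meet it and cites a prior intervention in which the rate rose from 5% to 30%. Because the answer is given when the device is fitted, it is normally on file before wear can fall short. The rule then removes a child whose result is known.

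At stake are information in a trial of 40 families per arm and, under conditions that the documents do not establish, the accuracy of the two proportions. The planned imputation does not clearly repair this. It is a sensitivity analysis, and nothing says that settled failures are held at not met.

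**Working it through.** **1. The plan's own figures.** Inputs from Sample Size and Power Calculation: 5% versus 35%, 30 per arm, 80% power, 25% dropout, significance level 0.05 (two-sided assumed).

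- Recruitment: 30 / (1 − 0.25) = 40 per arm, as stated.
- Exact power with Fisher's test or the Yates-corrected chi-square at 30 per arm: 78.8%, close to the stated 80%. The uncorrected chi-square gives 88.0% exactly.
- Normal approximation: z = [0.30√n − 1.96√(2 × 0.20 × 0.80)] / √(0.05 × 0.95 + 0.35 × 0.65).
 - n = 30: (1.643 − 1.109) / 0.524 = 1.02, power 84.6%.
 - n = 40: (1.897 − 1.109) / 0.524 = 1.50, power 93.4%.

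The step from about 85% to 93% is a ceiling. It needs every randomized child to have a determined outcome.

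**2. How many outcomes could be settled by screen time alone.** The invalid-wear count is not documented, so 4 to 10 of 40 per arm is an assumption. Settled failures = invalid-wear children × (1 − screen-time rate). A child who meets all three also meets screen time, so the lowest coherent rates are the all-three rates, 5% and 35%. Higher rates of 30% and 50% are shown for range.

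| Arm | Screen time met | Settled, of 4 | Settled, of 10 |
|---|---|---|---|
| Control | 5% | 3.8 | 9.5 |
| Control | 30% | 2.8 | 7.0 |
| Intervention | 35% | 2.6 | 6.5 |
| Intervention | 50% | 2.0 | 5.0 |

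This presumes that each of these children has a week-12 screen-time answer.

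**3. Is the complete-case proportion biased?** Take the intervention arm with 10 of 40 invalid and wear unrelated to outcome. The 30 valid children give 0.35 × 30 = 10.5 successes, or 35%. Over all 40:

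- Screen time met by 35%: 3.5 undetermined, bounds 10.5/40 = 26.3% to (10.5 + 3.5)/40 = 35.0%.
- Screen time met by 50%: 5 undetermined, bounds 26.3% to (10.5 + 5)/40 = 38.8%.

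The reported 35% lies within both ranges, so there is no bias in this case.

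At the opposite extreme, assume that every excluded child failed, with true rates of 14/40 and 2/40:

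- 4 excluded per arm: 14/36 = 38.9% and 2/36 = 5.6%, a difference of 33.3 points.
- 10 excluded per arm: 14/30 = 46.7% and 2/30 = 6.7%, a difference of 40 points.

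The true difference is 30 points. This extreme assumes the bias that it displays. It shows a mechanism and is not an estimate.

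**4. Why a half-repair is worse.** If wear is unrelated to outcome and the known failures are added while the undetermined children stay out, the intervention rate becomes 10.5 / (30 + 6.5) = 28.8%, or 10.5 / (30 + 5) = 30.0%, against a true 35%.

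**The case against.** The strongest reply is that the wear sentence sits within the accelerometer text, before screen time is introduced, and can be read as a validity rule for device measures only. How a composite is scored from partial data is often left to an analysis plan, and imputing the components and then deriving the composite would keep settled failures at not met automatically. These points have some force. The sentence never says that the composite is set to missing. But it stands under Primary Outcome, it says which preschoolers are included, and no other population is given for Aim 1. The protocol has therefore stated an inclusion rule and not left one open.

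Three stronger readings are tempting and are not supported:

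- A reader might infer that the rule overstates the proportions because most excluded children are failures. Most included children are failures too, 95% and 65% on the plan's assumptions. Overstatement requires excluded children to fail more often than included ones, and nothing in the documents says so.
- A reader might combine 35% meeting all three with the prior study's 30% meeting screen time and find 35% above the upper bound, (10.5 + 3)/40 = 33.8%. Those rates cannot hold in one population. With a coherent 35% for screen time the bound is 35.0%.
- A reader might treat the 25% allowance as invalid wear and conclude that most missing outcomes are recoverable. It is a dropout rate. A family lost before week 12 would usually have no screen-time answer either. Only 3 valid days out of 14 are needed, and Results reports one loss among 39 randomized, so invalid wear may be uncommon.

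**Conclusion.** The point holds as one about discarded information. On its plain reading, the rule removes children whose primary outcome is already known to be not met, and no other provision clearly restores them. The loss is certain for every such child, but their number cannot be derived from the documents.

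The power figures, about 85% at 30 per arm and 93% at 40, bound what could be gained. The real gain will be smaller, because the step from 30 to 40 represents dropout in the plan and because children who meet screen time but lack valid wear stay undetermined.

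Bias is possible but not shown. It depends on wear validity being related to guideline adherence, overall or differently in the two arms. The conclusion assumes that the wear sentence governs the Aim 1 analysis, and that the week-12 screen-time answer is usually available when wear fails.

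**What to change.** State that the wear criterion decides only whether the accelerometer-based activity and sleep components are observed. Then derive the composite in this order:

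- not met, if any observed component fails;
- met, only if all three components are observed and met;
- undetermined, otherwise.

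Use this derivation in the intent-to-treat and multiple-imputation analyses already planned under Exploratory Aims. Impute at component level, so that settled failures stay not met and only undetermined children are imputed. Report best and worst bounds, counting all undetermined children first as met and then as not met, and give the number of undetermined children per arm.

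Do not add known failures to the complete-case chi-square while leaving undetermined children out, because that pulls the rates down. The recovered outcomes should enter a comparison only together with the imputation.

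No new data are needed and the rule can be fixed before analysis. The cost is somewhat more analysis work, and the reported proportions may come out slightly lower.

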#### Secondary Outcome

Feasibility and acceptability are assessed by a weekly survey within the app. The parent reports how difficult or easy it was to achieve the goal, such as removing TV from the bedroom (Likert scale responses: range 1-5). Parents also rate their satisfaction with the app with regard to design, appeal, and functionality, and complete the System Usability Scale at week 6 and week 12, which can be used to assess overall usability of the app [41]. At the final visit, participants randomized to the intervention complete a 15-item survey to assess the acceptability and usability of app features and content, and overall participation. Responses from these questions will be combined with app usage data to evaluate the performance of these components for future iterations.

#### Exploratory Outcomes

##### Parent Report of 24-Hour Guideline Adherence

Parents will report how many days per week (range: 0-7) their child obtains at least 180 min/d of total PA and at least 60 min/d of MVPA. Staff members describe total PA as including any activity, such as slow or easy movement, based on direct report observations of preschooler’s movement [42]. These may include walking, light dancing, playing catch, and easy bike riding. MVPA includes any “huff and puff” activity that increases their heart rate, such as playing a sport, more intense dancing, and running. If parents have trouble discerning days, the staff will ask them about the past week. Furthermore, parents will be asked on average how much overnight sleep and time their child spends napping, in separate questions with free response options, which are summed for a total amount of sleep during the day. The sleep questions have demonstrated moderate correlations with accelerometry measures [43]. Parents are also asked about screen time (refer to “Primary Outcomes” section). We chose these questions based on national surveys of child PA [44] and surveillance efforts of child movement behaviors [40,45]. This information is gathered during the phone screening process, where trained staff members ensure parents consider both weekdays and weekends, and any changes due to nontypical weeks, to obtain accurate habitual behavior amounts. Screening questions related to total PA, MVPA, and sleep are repeated at week 6 and week 12.

